### Statistical analysis

First, we will perform a descriptive analysis of the demographic, nutritional and clinical parameters of the included patients. Specific data includes geriatric syndromes, full nutritional assessments, muscle strength (based on HGS), body composition, sleep questionnaires, CCI, and non-invasive hemodynamic parameters. Continuous data will be presented as mean ± SD and categorical data will be presented as proportion. Normality distribution will be tested by D’Agostino omnibus test. Patients will be classified according to clinical evaluation according to the cognitive deficit, frailty, nutrition status, stage of renal function (4 or 5) and the presence of sleepiness and poor quality of sleep. Exploratory analyses will include an association between any of the above-mentioned clinical diagnoses with the 2 outcomes: death or beginning of renal replacement therapy. These outcomes will be closely monitored by the study team in the routine visits or and/or by telephone contact. A *p* value < 0.05 will be considered significant. Analyses will be performed using SPSS 22.0 (SPSS Inc., Chicago, IL, USA) and *GraphPad Prism® software* (GraphPad Software, Inc., CA, USA).

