**Methods:**

AGNES is a prospective observational cohort that aim to investigate clinical, biochemical and demographic factors associated with RRT initiation and mortality of patients with CKD stage 4 or 5 who are aged 70 years and older. We plan to include 200 patients over 5 years. Clinically stable outpatients on conservative management for at least 6 months will be recruited from the Nephrogeriatric Clinic at the *Hospital das Clinicas da Universidade de Sao Paulo*, Brazil. Eligible patients are submitted to a full clinical examination, geriatric assessment, and blood test at baseline. Following the baseline visit the patients are being monitored during an observational follow up period of at least 12 months during which patients will be contacted in the clinic at their regular follow up or by phone until either RRT initiation or death occurs. This cohort includes evaluation of cognition by the education-adjusted 10-point Cognitive Screener (10-CS), frailty by Fried index score, a complete nutritional assessment (by body composition assessment, global subjective assessment and dietary intake), comorbidities by Charlson comorbidity index and biochemical markers including FGF-23 and Klotho.

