### Global geriatric assessment (GGA)

All participants are being submitted to a GGA at baseline, performed by the same physician. GGA includes a structured interview, physical examination, and a geriatric functional assessment. Geriatric domains assessed are functional status (daily life activities), nutritional status, physical health, cognition, depression, and social and family support [5].

The Katz Index of Independence in Activities of Daily Living (ADL) [6], validated to the Portuguese language [7] will be used to assess the functional status. The Katz index of ADL provides measures independence and need of assistance during bathing, dressing, toileting, transferring, continence, and feeding. Higher scores indicate more patient independence.

The Geriatric Depression Scale (GDS)-Short Form will be used to identify presence of depression and its severity [8]. This test yield scores that range from 0 to 15 with higher scores indicating higher depression probability.

The education-adjusted 10-point Cognitive Screener (10-CS) [9] assesses cognitive performance. Individuals with scores ≥8 are considered to have normal or near-normal cognition.

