### Pittsburgh sleep quality index (PSQI)

The PSQI is an instrument used to measure the quality and patterns of sleep in adults [25], validated to the Portuguese Language [26]. Seven domains are evaluated: subjective sleep quality, sleep latency, sleep duration, sleep efficiency, sleep disturbances, use of sleep medication, and daytime dysfunction over the last month. Patients are classified as poor sleepers or good sleepers when the sum of scores is > or < 5, respectively.

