### Power analysis

The sample calculation to obtain *p* < 0.05, with a cross-sectional design, and 80% of beta error, was calculated to require 197 individuals or 119 events. Based on the average monthly attendance of patients with the inclusion profile in the study and considering refusal and loss of follow-up in up to 20% of the sample, we plan to include this sample in 4.5–5 years.

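### The only association analysis described uses clinical classes, including CKD stage 4 versus 5; testing the scores and eGFR already collected would be more efficient at almost no cost

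*Protocol article*

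**What the plan says.** In Statistical analysis, "Patients will be classified according to clinical evaluation according to the cognitive deficit, frailty, nutrition status, stage of renal function (4 or 5" is followed by presence of sleepiness and poor sleep quality. The next sentence says that exploratory analyses will include associations of these diagnoses with two outcomes, death and RRT start. For testing, the section gives only this: "A *p* value < 0.05 will be considered significant".

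The classes and the finer data behind them are described elsewhere in Methods:

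- **Cognition** (Global geriatric assessment): a 10-point screener (10-CS) with one cut, "Individuals with scores ≥8 are considered to have normal or near-normal cognition".
- **Frailty** (Frailty index): a count of 0 to 5 criteria, grouped as 0, 1–2, and 3 or more.
- **Nutrition** (Nutritional assessment): 7p-SGA from 1 to 7, in three groups. BMI classes are also defined.
- **Sleep quality** (Pittsburgh sleep quality index): "Patients are classified as poor sleepers or good sleepers" by whether the sum is above or below 5.
- **Sleepiness** (Subjective sleepiness): eight Epworth (ESS) items scored 0 to 3, with no cut stated.
- **Kidney function** (Laboratory biomarkers): eGFR from the charts. Background places stage 5 below 15 ml/min/1.73 m².

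**The concern.** A class throws away differences between patients on the same side of a cut. When the finer measurement is on file, testing the class instead usually lowers power without saving any effort. That matters here because the cohort is small and slow to build: "We plan to include 200 patients over 5 years". The article's own limitations paragraph notes that this is not a large multicentre study.

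Stage 4 versus 5 is the clearest case. An eGFR of 16 and one of 29 share a class. Stage 5 mixes patients above and below 10, the level under which the Abstract says RRT is usually indicated. Distance from that level is an obvious candidate driver of RRT start. The Discussion promises factors independently associated with each outcome. If stage were the only kidney-function term in such models, eGFR differences within stage would stay uncontrolled.

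Two of the classes are also not fully defined. A PSQI sum of exactly 5 falls in neither sleep group, and no ESS cut is given for sleepiness. Using the scores avoids both problems.

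**Working it through.** **The plan's own figure.** Power analysis says the sample "was calculated to require 197 individuals or 119 events", "with a cross-sectional design, and 80% of beta error". It states no effect size, exposure prevalence or test, so 197 and 119 cannot be reproduced. At two-sided 0.05 and 80% power, several effects fit. With Schoenfeld's formula, a hazard ratio of about 1.67 with equal groups gives about 119 events, and 1.75 with a 30/70 split gives 120. A correlation of about 0.198 gives about 197 patients. None of these can be taken as the one used. The article therefore does not show whether the size was set for a class or for a score.

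**Assumptions.** Two-sided 0.05 (sidedness is not stated). 80% power for the test on the score (the article's wording is 80% beta error). A roughly normal score with a linear effect. Class shares and eGFR distributions are assumed, because the article gives none.

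**Two classes** (cognition, sleep quality, sleepiness). With share p in one class, efficiency relative to the score is E = φ(z_p)² / [p(1 − p)], and power after the cut is Φ[(1.96 + 0.84)√E − 1.96].

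- p = 0.5: 0.3989² / 0.25 = 0.637. Power: 2.80 × 0.798 − 1.96 = 0.27, giving 61%.
- p = 0.2: 0.2800² / 0.16 = 0.490. Power: 2.80 × 0.700 − 1.96 = 0.00, giving 50%.

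| Split | E | Loss | Power | 119 events act like | 197 patients act like |
|---|---|---|---|---|---|
| 50/50 | 0.637 | 36% | 61% | 76 | 125 |
| 30/70 | 0.576 | 42% | 57% | 69 | 113 |
| 20/80 | 0.490 | 51% | 50% | 58 | 97 |
| 10/90 | 0.342 | 66% | 37% | 41 | 67 |

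**Three classes** (nutrition, if 7p-SGA is meant). E is the squared correlation between an equally spaced class score and the underlying normal score.

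| Shares | Loss |
|---|---|
| 27/46/27 | 19% |
| 10/50/40 | 23% |
| 60/35/5 | 31% |
| 70/27/3 | 39% |
| 80/18/2 | 49% |

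**Frailty.** E is the squared correlation between the three-level class and the 0–5 count. Over binomial and beta-binomial counts with mean proportions of 0.3 to 0.5, E runs from 0.77 to 0.86, a loss of 14–23%. Power then falls from 80% to between Φ(2.80 × √0.77 − 1.96) = 69% and Φ(2.80 × √0.86 − 1.96) = 74%.

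**Stage 4 versus 5.** E is the squared correlation between the indicator eGFR < 15 and eGFR, over assumed distributions limited to 5–30.

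| Assumed eGFR | Share in stage 5 | Loss |
|---|---|---|
| Uniform | 40% | 28% |
| Normal, mean 17, SD 6 | 36% | 37% |
| Normal, mean 20, SD 6 | 21% | 46% |
| Normal, mean 22, SD 5 | 8.5% | 65% |

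**The case against.** The strongest reply is that the classes match the questions. The exploratory hypotheses concern clinical states such as frailty, cognitive deficit, protein-energy wasting and poor sleep quality, and most cuts come with the instruments. Associating a recognised diagnosis with an outcome is a legitimate analysis. A per-point slope answers a neighbouring question and needs a linearity assumption. The text is also one short section of a condensed article, and a fuller plan may say more. This is a fair case for keeping the classes. It does not remove the point, because the article does state an exposure form and it is the less efficient one.

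Three stronger readings are tempting, and the documents do not support them:

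- **That the scores are never analysed and every hypothesis loses power.** The text says what exploratory analyses will include, which is not exclusive. The Charlson index, Klotho and FGF-23 carry hypotheses of their own and are not among the classifications listed.
- **That a third to a half of the information is lost across the plan.** That range belongs to two-class cuts with roughly 20–50% in the smaller class. Frailty and 7p-SGA have three levels and usually lose less, while a rare class would lose more. The article does not tie nutrition status to 7p-SGA, and short ordinal scores are only loosely normal.
- **That RRT associations are confounded by eGFR.** No adjustment model or covariate list is given. Stage appears as a classification to be related to outcome, not as the adjustment term.

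**Conclusion.** The concern holds as a point about efficiency. It does not show that the analysis is invalid. The direction of the loss is clear under a broadly monotone, near-linear effect. Its size is not known, because no class shares are given and the figures rest on assumed distributions and linearity. Under those assumptions the two-class instrument cuts lose about 36–51% for splits from 50/50 to 20/80, the three-level items typically 14–23%, and stage 4 versus 5 anywhere from 28% to 65%. The confounding concern is conditional: it applies only if adjusted models include kidney function solely as stage. With about 200 patients, and allowance for "considering refusal and loss of follow-up in up to 20% of the sample", even the smaller losses are worth avoiding when the data are already in hand.

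**What to change.** In Statistical analysis, name the score as the main exposure in the association tests: 10-CS points, Fried count, 7p-SGA, PSQI and ESS, each per point or per SD, with a check for non-linearity. Use continuous baseline eGFR for kidney function, both as an exposure and in any adjusted model. Keep the clinical classes for baseline tables, survival curves and a secondary, clinically labelled analysis. State which nutritional measure defines nutrition status.

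This needs no new visit, assay or patient, only a few sentences, and they can be written before any outcome results are seen. The price is a linearity assumption, or a few degrees of freedom where a spline is used.

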## Discussion

We have initiated the recruitment of elderly patients with CKD stages 4 and 5 under treatment at the multidisciplinary outpatient clinic. This study will bring novel data on risk factors in the context of CKD in individuals with comorbidities and geriatric syndromes, a scenario that raises many unanswered questions about when and to whom indicate RRT. This cohort will allow for the assessment of clinical factors that potentially impact the risk of death. Furthermore, this study aims to characterize the clinical and demographic profiles of elderly patients with CKD not receiving dialysis. Ultimately, this study will help elucidating if the risk of mortality will be higher than the risk of not starting dialysis in this population and the factors independently associated with each one of these outcomes.

This study includes several strengths such as a multidisciplinary approach that brings clinical information beyond nephrology since geriatric syndromes and nutritional status will be assessed. To the knowledge of the authors, this is the first study on Latin America with this profile.

Elderly patients with advanced CKD faces a high risk for common geriatric conditions such as cognition deficit [29]. It is known that cognitive function broadly deteriorates as CKD progresses from stage 1 to stage 5. As CKD progresses, deficits in executive functioning, verbal fluency, logical memory, orientation, and concentration become more evident. People with end-stage kidney disease manifest significant cognitive deficits, along with delayed and immediate memory, visuospatial impairment, and overall cognitive impairment [30]. Cognition, however, does not seem to increase the risk for CKD progression [31]. In addition, it has been demonstrated that cognition declines faster in dialysis patients compared with CKD patients receiving conservative treatment, and in hemodialysis patients compared with peritoneal dialysis patients [32].

Frailty and poor functional status are risk factors for adverse patient outcomes that may be useful additions to prognostic tools in patients with CKD [33, 34]. Recent evidence supports the prognostic significance of frailty for functional decline and poor health outcomes in patients with CKD [35]. Frailty is also associated with bone loss among patients with CKD [36]. Therefore, our study will add body to the literature showing if frailty will predict death or dialysis initiation in elderly patients with CKD.

The transmembrane form of α-Klotho serves as a co-receptor for the fibroblast growth factor (FGF)23 and may have independent homeostatic functions as a hormone [37]. In patients with CKD, there is a disruption of the FGF23-αKlotho axis manifesting in deficient klotho expression and FGF23 excess. Multiple lines of evidence show that the anti-aging and cognition-enhancing protein Klotho fosters neuronal survival, increases the anti-oxidative stress defense, and promotes remyelination of demyelinated axons [38]. Klotho and FGF-23 have been already associated with cardiovascular disease mortality in patients with CKD [39]. A randomized Italian trial showed that higher plasma klotho concentration was associated with lower likelihoods of frailty in individuals aged 65 years or over [40]. This finding highlights the importance of Klotho measurement in elderly patients with CKD.

Sarcopenia has been associated with mortality in patients with CKD in both conservative management [41] and dialysis [42]. Nutritional assessment in the current study will provide valuable information that might help to understand risk factors for death and the beginning of renal replacement therapy. In addition, we will be able to understand dietary patterns in the elderly population with CKD, and analyze associations of nutritional status with functional status, frailty and mortality.

Sleep disorders are common among patients with CKD, who experience both poor sleep quality and a lower amount of sleep when compared to the general population [43]. Indeed, sleep duration has been associated with progression to end-stage renal disease [44]. However, most studies were confined to dialysis patients and there is scarce information on sleep disorders among CKD patients within the conservative management scenario. Since sleep disorders are highly prevalent in patients with CKD, and has been associated with fluid overload [45] and mineral and bone metabolism [46] and higher age elderly individuals present, naturally, a reduction of sleep duration, the current study might contribute to the body of the literature in this field.

The results and interpretation of this study should consider some limitations: first, as this is not a large multicenter study the number of patients is relatively know. Second, polysomnography will be available only for a subset of patients. Third, the choice of starting renal replacement therapy is a shared-decision and many factors not investigated within the study such as family and social support may bias this outcome. However, we aim for a real-world study that likely will mimic the usual clinical practice, and considering that it is unethical to randomize patients to start dialysis or not regardless of their wishes, the current design is the one achievable.

In summary, this clinical study intends to address a common challenging situation in renal care of elderly individuals with CKD namely the choice between initiating renal replacement therapy vs. continue with conservative management. One of many questions we hope to answer is: Who are at higher risk of death when initiating dialysis in elderly patients and in whom would conservative management be more appropriate? However, we will evaluate not only survival benefits but also patient-reported outcomes including parameters related to health benefits and quality of life. The identification of features associated with patient survival, health benefits and quality of life may inform treatment strategies for better management of elderly patients with CKD. Ultimately, this study will address what, for whom and when considering a given treatment for individuals of the same age but with different functional state will result in opposite outcome.

## Data Availability

The datasets are being generated since the study is ongoing and are not publicly available but are available from the corresponding author on reasonable request.

## Abbreviations

7p-SGA: 7-point subjective global assessment
10-CS: 10-point Cognitive Screener
ADL: Activities of Daily Living
AGNES: Aging Nephropathy Study
BIA: Bioelectrical impedance
BIS-1: Berlin initiative study
BMI: Body mass index
CCI: Charlson Comorbidity Index
CF: Calf circumference
CES-D: Center for Epidemiological Studies Depression
CKD: Chronic Kidney Disease
ESS: Epworth Sleepiness Scale
eGFR: Estimated glomerular filtration rate
GDS: Geriatric Depression Scale
GGA: Global geriatric assessment
FGF-23: Fibroblast growth factor 23
HGS: Handgrip strength
IPAC: International Physical Activity
MUAC: Right mid-upper arm circumference
PTH: Parathyroid hormone
PSQI: Pittsburgh Sleep Quality Index
RRT: Renal replacement therapy
